## Abstract

**Background:**

Down syndrome (DS) is a common genetic disorder resulting from an extra copy of genetic material from all or part of chromosome 21. Individuals with DS have a higher burden of co-occurring structural birth defects, neurocognitive delay, and chronic health conditions when compared to those without DS, as well as a 10 to 20-fold excess risk for acute leukemia (AL). Few studies have reported the late effects of cancer treatment in DS-AL survivors, and even fewer have compared outcomes to children with DS and no cancer history. The Children’s Oncology Group study ALTE22C1 was developed to address this knowledge gap.

**Methods:**

This study leverages both registry and site-based DS-AL survivor recruitment and a prospective/retrospective cohort design to compare chronic health conditions and neurocognitive outcomes experienced by DS-AL survivors to age and sex-matched individuals enrolled to a DS cohort for which cancer is exclusionary. Survivors 6–39 years old, ≥ 3 years from end of AL treatment, and in remission are eligible. Participants complete a medical conditions survey and neuropsychological battery by parent proxy and may also participate in an in-person physical and neurocognitive assessment. Biological samples are collected to evaluate molecular features associated with outcomes.

**Discussion:**

This cooperative group study will identify the prevalence and severity of medical and neurocognitive outcomes in DS-AL survivors compared with non-DS AL and DS controls without cancer history. Results are anticipated to inform clinical practice guidelines for DS-AL survivors and improve survivor outcomes through mitigation of outcome disparities in this vulnerable population.

**Trial registration:**

Children’s Oncology Group study ALTE22C1 is registered under the ClinicalTrials.gov identifier NCT05702645.

## Background

Survival from childhood and adolescent cancer has increased significantly in the past several decades, from under 50% in the 1970s to over 80% today [1]. This remarkable achievement has resulted in an exponential increase in the number of childhood cancer survivors living in the United States, projected to exceed 500,000 by this year [2]. However, the price of cure includes a significant burden of treatment-related morbidities. Seventy percent of adult survivors are estimated to suffer from one or more severe, disabling, or life-threatening chronic health conditions (CHC) or 'late effects' that significantly and negatively impact their quality of life [3, 4]. Down syndrome (DS) is a genetic disorder that results from a constitutional trisomy of chromosome 21. This disorder is associated with distinguishing phenotypic features, intellectual disability, co-occurring structural birth defects, and an increased risk for CHC. Children with DS are also at increased risk for developing hematologic malignancies, with a 10 to 20-fold excess risk in comparison with the general population, so that between 1:100 and 1:150 children with DS will develop acute leukemia (AL), [5, 6] predominantly B-lineage acute lymphoblastic leukemia (ALL) or acute myeloid leukemia (AML), composing 2% of all pediatric ALL cases and 15% of all pediatric AML cases. During treatment for AL, children with DS experience excess acute cancer therapy-related toxicities compared to their non-DS peers with ALL and AML [7–9].

In the absence of DS, AL treatment confers a substantial risk for late effects. Among 272 AML survivors enrolled to the Childhood Cancer Survivor Study (CCSS), the cumulative incidence of CHC at 20 years from diagnosis was 50%, of which 16% were severe, compared with only 6% of sibling controls [10]. Similarly, at 25 years from diagnosis, the cumulative incidence of CHC among ALL survivors enrolled to CCSS was 65%, of which 21% were graded as severe [11]. A meta-analysis of neurocognitive sequelae of childhood ALL provides consistent evidence that cancer therapy impacts intellectual function even in the absence of radiation exposure, particularly with respect to attention, working memory, and processing speed [12, 13], although less is known regarding the neurocognitive sequelae of AML treatment [14].

Despite the well-described late effects associated with childhood AL treatment and the known excess acute toxicities experienced by children with DS-AL, little is known regarding the prevalence of long-term therapy-related CHC and neurocognitive outcomes in survivors of DS-AL. As a result, the National Down Syndrome Society and Lumind, IDSC identified the impact of leukemia and its therapy on neurodevelopmental, health, and quality of life outcomes as one of the key scientific gaps in DS research [15].

The Children’s Oncology Group (COG) study ALTE22C1 (ClinicalTrials.gov Identifier: NCT05702645) was developed to address this unmet need, with the overarching hypothesis that DS-AL survivors are at increased risk for CHC and neurocognitive deficits compared to persons with DS and no cancer history.

## Methods/design

### Aims

The primary aim of this study is to determine the prevalence, type, and severity of CHC in survivors of DS-AL and to compare CHC outcomes to those of frequency-matched individuals with DS with no cancer history. Secondary aims include characterizing post-treatment clinical outcomes of DS-AL, determining prevalence and severity of parent-reported neurocognitive outcomes in survivors of DS-AL compared with frequency-matched individuals with DS without leukemia, determining health-related quality of life in survivors of DS-AL, and identifying clinical risk determinants of CHC, neurocognitive outcomes, and clinical outcomes in survivors of DS-AL. Biological and molecular correlations will be tested in exploratory aims, i.e., we will test whether structural birth defects and genetic alterations associated with etiology also demonstrate associations with CHC in DS-ALL, and whether telomere length is associated with in-person-assessed neurocognitive outcomes in DS-ALL.

### Study design

Children’s Oncology Group ALTE22C1 utilizes a retrospective/prospective observational cohort design with a control group comparison. For survivors of AL, study participation is divided into three parts, with a workflow that relies on centralized Data Coordinating and Neuropsychology Centers to minimize responsibilities of COG site-based research staff. Study participants, or his/her designee, provide separate consent for participation in Parts 1, 2, and 3. See Fig. 1 for the study design schema.

**Fig. 1 Fig1:**
[figure not shown]
Study Design Schema for COG ALTE22C1. ^See Table 1 for list of measures

Part 1 is conducted remotely through REDCap® [16, 17] (with a paper alternative) and consists of a medical record release, medical condition survey (completed by parent proxy and verified by medical record review), and saliva sample. Part 1 also includes a neurocognitive battery completed by parent proxy and designed to evaluate executive function and self-regulation, social competence, problem behaviors, autism spectrum behavior, communication, adaptive behavior, and quality of life. The measures included and their target area of assessment are shown in Table 1 [18–23]. Part 2 is focused on in-person assessments and requires local COG site activation of this central-IRB-approved protocol. For Part 2, consent is obtained by COG site personnel. Resources are available to sites that support inclusion in research of persons with intellectual disabilities [24], including a visual break board for survivors to direct the pace of the consent conversation and request a pause or stop if needed (Fig. 2) [25]. Part 2 comprises an in-person, COG Long-Term Follow-Up Guidelines [26]-informed and Down Syndrome Guidelines [27, 28]-informed long-term follow-up visit. Results of the clinic visit, including diagnosis and treatment information, complete review of systems, vital signs and anthropometrics, Tanner staging, list of medication, and results of any laboratory or diagnostic tests, are reported by the COG site-based research team via REDCap® to the central data coordinating center. Part 3 comprises a comprehensive, in-person neurocognitive evaluation on a subset of ALL survivors and research blood draw, also requiring COG site activation in addition to COG site-based training. The COG site-based research team administers the NIH Toolbox Cognitive Battery (NIH-CB) using a study-supplied tablet. The NIH-CB is validated in persons with intellectual disability [29, 30] and includes seven tests: Flanker Inhibitory Control and Attention, Dimensional Card Sort, List Sorting Working Memory, Oral Reading Recognition, Pattern Comparison Processing Speed, Picture Sequence Memory, and Picture Vocabulary. The Part 3 required research blood draw is banked for future assessment of leukocyte telomere length by telomere flow-fluorescence in situ hybridization (FISH) [31].

**Table 1 Tab1:** Part 1 and Part 3 Neurocognitive Measures Included in COG ALTE22C1

Neurocognitive Measures	Abbreviation	Target Assessment
Part 1: Parent Proxy		
Behavior Rating Inventory of Executive Function, 2nd ed	BRIEF-2	Executive functioning and self-regulation
Vineland Adaptive Behavior Scales, 3rd ed	Vineland-3	Adaptive behavior
Social Communication Questionnaire	SCQ	Autism spectrum disorder screening
Nisonger Child Behavior Rating Form	NCBRF	Social competence and problem behaviors
Children’s Communication Checklist, 2nd ed	CCC-2	Communication and language impairment screening
Pediatric Quality of Life Inventory, Generic Core Scales v4.0	PedsQL	Health related quality of life
Part 3: Direct Assessment		
NIH Toolbox Cognitive Battery	NIHTB-CB	Executive function: inhibitory control, cognitive flexibility, attention

**Fig. 2 Fig2:**
[figure not shown]
Visual Break Board. This visual break board is adapted from Kidney, et al., 2014 and is available to participating sites to facilitate subject recruitment and promote inclusion in research of neurodivergent populations. The following instructions are provided to support its use. *How to use this tool*: Prior to initiating a consent discussion, provide the patient with this ‘stoplight’ sheet or card. Advise him/her that you will be discussing a research study and would like to make sure that he/she is comfortable and understands what is being said. Let the patient know that he/she may indicate Red, Yellow, or Green any time during the discussion to indicate: • ‘Stop, I would like to end this conversation,’ • ‘Pause, I need a break,’ or • ‘I’m OK, please keep going’• Pause periodically and prompt the patient to use the board to provide you with an indication to stop, pause, or go on.

### Study setting

This study leverages the COG cooperative group infrastructure. The COG is a member of the National Cancer Institute-funded Community Oncology Research Program and the National Clinical Trials Network, which includes over 220 academic and community hospitals that care for ~ 90% of children with cancer diagnosed in the United States [32].

### Recruitment, population, and eligibility

A unique feature of this observational survivorship trial is the hybrid recruitment approach that leverages the COG Childhood Cancer Research Network (ACCRN07) and Project EveryChild (APEC14B1) research registration and biobanking protocols [33, 34]. Potential participants with DS-AL are identified and recruited by two mechanisms run in parallel: 1) The Coordinating Center conducts centralized recruitment of patients that have consented to recontact and were enrolled to either ACCRN07, APEC14B1, and/or AEPI20N2 The DS-ALL Deep Phenotyping Project: Evaluating the Association Between Co-occurring Birth defects and ALL Risk in DS; 2) Site-based prospective recruitment at COG sites that have activated the study protocol (only for subjects not enrolled to any of the above registries or studies).

Eligible survivors are those with DS-AL who are ≥ 6 years old and < 40 years old, in remission, at least 36 months off primary cancer treatment, and able to understand either English or Spanish. Bone marrow transplant recipients are excluded (see Table 2). A diagnosis of Down syndrome is required and may include any of the three recognized types: trisomy 21 resulting from chromosomal nondisjunction (most common), translocation (the patient has 46 chromosomes, but all or part of an additional copy of chromosome 21 is attached to another chromosome), or mosaicism (trisomy 21 that is present in only a fraction of cells). All participants to ALTE22C1 must be a survivor of either ALL or AML/myeloid leukemia of DS (ML-DS) requiring treatment with chemotherapy and may not have had any other cancer diagnosis other than transient abnormal myelopoiesis. Based on the racial and ethnic distribution of childhood leukemia in the United States, the sample is expected to be 70% White, 10% Black, 20% other or multi-race, and about 20% Hispanic (estimates derived from the Surveillance Epidemiology and End Results Program).

**Table 2 Tab2:** Eligibility Criteria for COG ALTE22C1

Inclusion Criteria
• Age ≥ 6 and < 40 years at the time of enrollment
• Diagnosis of Down syndrome
• Survivor of ALL or AML treated with chemotherapy for their cancer diagnosis
• Completed treatment at least 36 calendar months prior to enrollment
• Life expectance > 1 year
• English or Spanish speaking
Exclusion Criteria
• History of hematopoietic stem cell transplant
• History of another cancer either prior to or subsequent to the ALL/AML diagnosis
• Parent or guardian unable to complete the required forms

The comparison population (‘DS controls’) are active participants in an ongoing research study cohort of children and young adults with DS. Recruitment to this study began in 1989 as a population-based case–control study conducted in the five-county metropolitan area of Atlanta and has since expanded recruitment to sites across the United States. Recruitment and enrollment methods to this study are described previously [35–38]. Controls will be frequency-matched to cases by age, sex, and, when possible, race and ethnicity.

### Role of coordinating centers

The Data Coordinating Center recruits and consents to Part 1 study activities and provides participants with Part 1 study materials. The plan for patient approach is first communicated and cleared through the COG institution of record in the form of an email notification that includes the affiliated subject’s COG ID number. The site has an opportunity to decline or postpone subject approach: 14 calendar days following the date of site notification, if no communication of concern has been received from the site, the Data Coordinating Center mails the recruitment packet directly to the survivor’s email or physical address followed by a phone call check-in approximately two weeks later. In addition, the Data Coordinating Center tracks all potential and enrolled participants, and, for enrolled participants only, ensures that study data and samples are collected in a timely fashion and that participants receive a reimbursement associated with the completion of each of the three study parts. The role of the Neuropsychology Coordinating Center is to ensure that Part 1 neurocognitive assessment data are collected and are complete, as well as to interpret results and prepare and return an abbreviated summary of the results to the family. The Neuropsychology Coordinating Center also provides the COG site with Part 3 NIH Toolbox training in addition to Part 1 neurocognitive test result interpretation.

### Study outcomes

The primary outcome is occurrence of CHC by category, organ system, and grade using the Common Terminology Criteria for Adverse Events (CTCAE), for both DS-AL survivors and DS controls. Secondary outcomes include clinical outcomes from the LTS visit, with laboratory and diagnostic tests categorized as ‘normal’ or ‘abnormal,’ and neurocognitive outcomes measured by standardized caregiver ratings (raw and standardized score as well as proportion ‘at the floor’ in each comparison group). Exploratory outcomes include raw and standardized scores as measured by the NIH Toolbox-neurocognitive battery.

### Sample size and power calculations

In a pilot study, we observed a higher likelihood of acquired cataracts among DS-AL survivors compared to DS controls, possibly related to steroid exposure during leukemia treatment (p-value = 0.03, all cases were DS-ALL survivors treated with steroids), and a higher likelihood of any cardiovascular or cerebrovascular event among DS-AL survivors compared to DS controls, possibly related to anthracycline exposure during leukemia treatment (p-value = 0.01, all cases were anthracycline-exposed). Based on these differences, with a sample size of 200 DS-ALL survivors and 200 DS controls, we will have 80% power to detect a hazard of 0.046 or 0.084, assuming a 2-sided alpha of 0.05 and an exponential baseline hazard of 0.062. With a sample size of 100 DS-AML survivors and 100 DS controls under the same assumptions, we will have 80% power to detect a hazard of 0.040 or 0.096. Based on the findings of Roncadin et al., [39] we will have 90% power to detect a 10-point difference in mean score for adaptive behavior. Assuming an expected standard deviation (SD) of 20 based on published data using the PedsQL to assess quality of life in populations with intellectual disabilities in comparison to those without disabilities [40], we will have 80% power to detect a difference in the mean scores of at least 4 to 6 points between DS-AL survivors and DS controls, sufficient to permit differentiation of healthy from acute or chronically ill subjects [41].

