## Discussion

ALTE22C1 is an ongoing multisite study open through the COG cooperative group that will compare the CHC and neurocognitive outcomes in DS-AL survivors, compared to persons with DS and no cancer history. The hybrid recruitment design leverages both COG patient registries as well as site-based recruitment of non-registry participants, thus supporting the collection of both patient-reported outcomes and data from in-person clinical assessment, in addition to reducing potential selection bias associated with exclusively registry-based recruitment. The steady pace of accrual since study launch suggests support from a motivated patient population as well as suggesting benefit to a study design that supports remote participation and that minimizes burden on participating COG sites.

There is a substantial dearth in our understanding of the long-term impact of cancer treatment in this vulnerable population. To date, the published data have compared late effect prevalence in this at-risk population to non-DS survivors of AL, which disregards the effect of the baseline excess risk for CHC experienced by individuals with DS. For example, the CCSS compared CHC in 154 DS-AL survivors to non-DS survivors matched by diagnosis, age at diagnosis, race/ethnicity, sex, radiation, and chemotherapy exposures, indicating that DS-AL survivors (median age 20 years, range 10–48 years) were at greater risk for serious CHC and ≥ 3 CHC than non-DS AL survivors, with a 25 year CHC cumulative incidence of 83% vs. 69% [49]. Similar results were seen in a smaller cohort of DS-AML survivors [50]. One study evaluated neurocognitive outcomes in DS-AL survivors vs. DS children without AL and found greater deficits in verbal intelligence, spelling, receptive and expressive vocabulary, visual-motor skills, and adaptive function [39]. In a more recent study that compared neurocognitive outcomes between 117 DS controls and 43 DS-AL survivors, differences were observed between the groups in completion rates for executive function and processing speed measures as well as in performance and rating measures of executive function [51].

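### No stated group size gives 80% power for a 4-point PedsQL difference, and the detectable hazards rest on an unstated event share of about 82–84% that ages 6 to under 40 are unlikely to supply

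*Protocol article*

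**What the plan says.** All the power figures stand in the protocol article under Sample size and power calculations.

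- **CHC, ALL.** After citing pilot differences in cataracts and in cardiovascular or cerebrovascular events, the article states: "we will have 80% power to detect a hazard of 0.046 or 0.084, assuming a 2-sided alpha of 0.05 and an exponential baseline hazard". The baseline value is 0.062, and the groups are 200 DS-ALL survivors and the same number of controls.
- **CHC, AML.** "With a sample size of 100 DS-AML survivors and 100 DS controls under the same assumptions", the detectable hazards are 0.040 or 0.096.
- **PedsQL.** With an SD of 20, "we will have 80% power to detect a difference in the mean scores of at least 4 to 6 points between DS-AL survivors", the other group being the DS controls.

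Other sections fix the conditions under which these figures must hold:

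- Study outcomes: "The primary outcome is occurrence of CHC by category, organ system, and grade".
- Eligibility (Table 2): survivors enrol from age 6 to under 40, at least 36 months after treatment.
- Statistical analyses: survivors without an event are censored at enrollment and controls at their last data update. Leukemia diagnosis is a time-varying exposure. Mean scores are compared by a two-sided, equal-variance t-test at 0.05, for DS-AL survivors and for DS-AL subgroups, each against DS controls.

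**The concern.** A PedsQL detectable difference follows from SD, group size, alpha and power alone, so it can be checked directly. Its lower end does not come back.

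The power of a hazard comparison depends on the number of events. The article gives no event count, follow-up time, age distribution or time unit for the hazard. The quoted hazards lie close to what the group sizes would give if nearly everyone had an event. That sits badly with a cohort that may enrol at age 6 and whose survivors are censored on that day.

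At stake is the reading of null results. A PedsQL result that is null in the AML group, or a CHC result that is null for one organ system, could be taken as adequately powered in a study meant to inform survivorship guidelines.

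**Working it through.** **PedsQL**

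Inputs: SD 20, two-sided alpha 0.05, 80% power. Groups are 200 (ALL), 100 (AML) and 200 + 100 = 300 (all AL). Equal numbers of controls are stated for ALL and AML and assumed for all AL.

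Detectable difference = (1.960 + 0.842) × 20 × √(2/n).

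| Comparison | Detectable at 80% | Power at 4 points | Power at 6 points |
|---|---|---|---|
| AL, 300 vs 300 | 4.57 | 69% | 96% |
| ALL, 200 vs 200 | 5.60 | 52% | 85% |
| AML, 100 vs 100 | 7.92 | 29% | 56% |

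The 6-point end is delivered for AL and ALL. For 4 points, n = 2 × 2.8016² × 20² / 4² = 392.4, so 393 per group. Exact t quantiles change little (394 per group).

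**Hazards: reproducing the stated figures**

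Inputs: baseline 0.062, alternatives 0.084 and 0.046 (400 subjects), 0.096 and 0.040 (200 subjects), two-sided alpha 0.05, 80% power. The time unit is not stated; per year is assumed.

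Schoenfeld events for 1:1 groups = 4 × 2.8016² / (ln HR)².

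| Hazard | HR | Events needed | Share of subjects |
|---|---|---|---|
| 0.084 | 1.355 | 341 of 400 | 85% |
| 0.046 | 0.742 | 353 of 400 | 88% |
| 0.096 | 1.548 | 165 of 200 | 82% |
| 0.040 | 0.645 | 164 of 200 | 82% |

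The shares move with rounding of the hazards: for 0.046, from 82% at 0.0455 to 95% at 0.0465. Solving the other way, the detectable hazard is 0.062 × exp(±2.8016 × √(4/(N × share))). A single share between 82.0% and 84.1% returns all four stated hazards to three decimals. At 83% they are 0.0843, 0.0456, 0.0958 and 0.0401. The figures are therefore mutually consistent.

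At 0.062 per year, that share requires −ln(1 − 0.82)/0.062 = 27.7 to −ln(1 − 0.841)/0.062 = 29.7 years at risk for every subject.

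**Hazards: power under explicit follow-up**

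If time at risk is uniform from a to b, the event share in a group with hazard λ is 1 − (e^(−λa) − e^(−λb)) / (λ(b − a)). Average the two groups' shares, multiply by N to get events d, and take power = Φ(½ √d |ln HR| − 1.96). The follow-up distributions are assumptions, because the article gives none.

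| Time at risk (uniform) | 0.084 | 0.046 | 0.096 | 0.040 |
|---|---|---|---|---|
| 6–40 years, from birth | 75% | 68% | 78% | 70% |
| 3–25 years | 65% | 56% | 68% | 57% |
| 18–40 years, from birth | 80% | 75% | 82% | 76% |

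Example, first cell: shares 0.713 (control) and 0.801 (survivor), d = 200 × (0.713 + 0.801) ≈ 303, power 75%.

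Counting from birth flatters the design, since exposed time begins only at leukemia diagnosis. Under the first row the hazards detectable at 80% become about 0.086/0.044 (ALL) and 0.097/0.038 (AML).

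**What 0.062 can refer to**

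At 0.062 per year, 1 − e^(−0.062 × 20) = 71% of controls would be affected by 20 years. That does not fit a single condition such as cataracts.

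**The case against.** The strongest reply is that the hazards are not a miscalculation. One event share of about 83% reproduces all four, and a condensed article may leave that assumption to the full protocol. This stands: the hazards are not an arithmetic slip. What remains is that the share they need fits poorly with the age range and censoring rule printed in the same article.

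A reader might infer that the follow-up cannot deliver 80% power at all. The documents do not support that. If every subject had the same time at risk, with each group at its own hazard, the requirement would be 26.9 years for 0.084, 23.1 for 0.096, 35.4 for 0.040 and 40.6 for 0.046. Only the last exceeds the age limit. The study hypothesis is of increased risk, and a mostly adult cohort would reach about 80–82% for the two harm-direction hazards. The correction to the hazards is also small, about 0.001 to 0.002.

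A reader might also set the Discussion's figure for DS-AL survivors, "with a 25 year CHC cumulative incidence of 83% vs. 69"%, against 0.062 and conclude that the true effect is too small to detect. That does not follow. The figure comes from an external cohort compared with non-DS survivors, and the endpoint and time unit of 0.062 are not given. Nor can a specific detectable HR for one organ system be stated, because the article gives no control rate for any single condition.

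On PedsQL, the 4-to-6 claim is worded for DS-AL survivors, not for AML, and both 4.6 and 5.6 lie inside that range. So only the lower bound is wrong as printed. The AML figure still matters because the analysis section plans subgroup comparisons with controls.

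**Conclusion.** The point holds in two parts of different strength.

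The PedsQL lower bound is wrong on the article's own SD and test. The smallest difference detectable at 80% is about 4.6 points with all survivors, if controls are equal in number, and 5.6 for ALL. The planned AML comparison detects only about 7.9.

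The detectable hazards depend on an unstated and demanding event share. With ages spread over 6–40, power is more plausibly 68–78%, and 56–68% with 3–25 years at risk. These figures assume a per-year hazard, exponential times, 1:1 groups and the stated uniform follow-up. An older cohort would close the gap in the harm direction only.

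The endpoint behind 0.062 is not identified. If it is an overall CHC rate, as its size suggests, the stated power does not carry over to comparisons by condition or organ system, which the primary outcome includes.

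**What to change.** No change in sample size is needed.

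1. Restate the PedsQL differences detectable with 80% power as about 4.6 points (AL), 5.6 (ALL) and 7.9 (AML), with the number of controls in each comparison.
2. Recompute the detectable hazards, or the power at the stated hazards, from the expected age and follow-up distribution. State the time unit, time origin and expected events. If ages are uniform on 6–40 and counted from birth, for example, the hazards are about 0.086/0.044 (ALL) and 0.097/0.038 (AML).
3. Name the CHC endpoint to which 0.062 refers and how it relates to the pilot differences cited before it.
4. Say that the stated power does not extend to single-condition or organ-system comparisons.

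The cost is a revised paragraph with somewhat less favourable figures.
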